### Inclusion Criteria

Families that are referred for treatment to the clinical practice will be screened using a questionnaire for behavioral problems, the Eyberg Child Behavior Inventory (ECBI) [44] and a questionnaire about parental stress (*opvoedingsbelasting vragenlijst* [OBVL]; in Dutch) [45]. All families that are referred will be required to fill out both questionnaires on the web, where their scores are checked to see whether they meet the inclusion criteria. The clinical cutoff score for the ECBI is >131 according to US norms, meaning that all scores >131 will be included [46]. For OBVL, a T score of ≥60 is considered problematic or even clinical, thus counting as the cutoff score.

### Exclusion Criteria

A potential participant who meets any of the following criteria will be excluded from participation in this study:

A child with severe physical impairment, such as deafnessA child with a mental disability (IQ<60)An unsafe home situation, where home displacement is indicatedChild or parent with problems requiring personal health care, such as suicidality, or parents with problems with aggression regulation or addictionParents known to have severe problems with motion sickness

It should be noted that IQ will not be tested during the screening; rather, a clinical judgment will be made by the therapist or professional during intake.

### Study Design

The study will use a nonconcurrent multiple baseline SCED across the 15 participants. This means that 15 individual cases will be analyzed following the same design structure. The design has been reported according to SPENT (Standard Protocol Items: Recommendations for Interventional Trials extension for N-of-1 trial protocols) guidelines [47]. SCEDs are often implemented to determine whether a causal relationship exists because of the introduction of an independent variable to the dependent variable [48]. In addition, it is frequently used when attempting to answer questions regarding the addition of a component to an intervention [49]. In terms of this study, this means that we will evaluate whether the addition of a VR element will increase positive parenting skills through multiple baseline SCEDs.

SCEDs can be used to both evaluate treatment effects for individuals and assess the efficacy of individualized treatments [48]. Although SCEDs are often compared with a case study design, there is a clear distinction: SCEDs require deliberate manipulation of an independent variable, and results from SCEDs are usually both visually and statistically analyzed [50,51]. Another clear distinction from other designs is that SCEDs differ from experimental designs that are based on comparing groups; the manipulated variable in a SCED refers to repeated measurements of an individual who is assigned to different treatments rather than the manipulated variable being evaluated by assigning multiple individuals to different groups [50].

Strong SCEDs can be characterized by three dimensions: (1) the design is divided into phases, (2) the design contains random assignment, and (3) the design should be replicated. Incorporating these dimensions improves the internal validity of the study and minimizes the possibility of history and maturation affecting the treatment effects [50]. These dimensions are incorporated into this study (Figures 1 and 2). First, the building blocks of a phase design can be divided into a baseline phase (A) and a treatment phase (B), with each phase containing multiple measurements. This can be made more complex by, for example, adding another treatment phase (C). Second, the phase design can be randomized by having different starting points for the treatment phase. In addition, a minimum of 3 measurement points is required per phase. In this study, randomization of the length of phases is used, which is increasingly considered important to make valid inferences about results. Third, the ways in which replication can occur is 2-fold: simultaneous replication entails conducting multiple phase designs at the same time, and sequential replication entails conducting multiple SCEDs to test the generalizability of the results. When both forms of replication are used, we speak of a hybrid design, which is called a nonconcurrent multiple baseline design, where partial temporal overlap is implied [50]. To adhere to these 3 dimensions and maximize internal validity, this study will use a nonconcurrent multiple baseline design.

The strength of SCEDs, when designed with phases, randomization, and replication, is that they allow for the comparison of an individual in different phases of treatment, thus demonstrating progression while also being able to compare the treatment effects of multiple individuals at different times [50]. Analyses are conducted both visually and statistically, thus providing an aggregated overview of individual and group treatment effects. SCEDs allow for a unique perspective where clinical practice lends itself to research rather than the other way round. An individual is personally followed, and data points are manipulated to provide results rather than their treatment conditions being manipulated. Subsequently, group comparisons can be performed on the basis of an individual’s own trajectory. Considering the fact that PCIT has already been widely researched, using the current design allows for an in-depth analysis of the newly implemented VR element in the treatment.

The multiple baseline SCED in this study is set up as shown in Figure 1. First, informed consent will be signed after families have received verbal and written information about the study. Second, participants will be dually randomized (by an external party) to determine their baseline period (4, 5, or 6 weeks of baseline measurements; phase A) and the addition of their VR element (VR at the start of CDI and after 3 or 6 sessions of CDI; phase B). After randomization, participants will start with phase A—the baseline period. Parents will electronically fill out the questionnaires weekly regarding child disruptive behaviors and parental stress using the ECBI and the short version of the OBVL. At the end of phase A, a pretreatment assessment will be performed. In this assessment, parents will be required to electronically fill out more questionnaires regarding both child and parental factors (Figure 1; see the *Assessment Instruments* section). In addition, the researcher will also make a video recording of the parent and child playing in 3 play situations (child-led play [CLP], parent-led play [PLP], and clean up [CU]), which will consequently be coded using the Dyadic Parent-Child Interaction Coding System (DPICS) [52]. Following this, in phase B, the intervention phase starts. Depending on their random allocation, families will start off with PCIT with or without the VR element. Once again, they will electronically fill out the ECBI and OBVL-*kort* (OBVL-K) weekly, and they will also register their homework completion and (if applicable) their VR completion sheets. During the PCIT sessions, PCIT therapists will register the parental progress weekly by coding 5 minutes of playtime with the DPICS. Once families reach CDI completion, they will move on to phase C, which is the parent-directed interaction (PDI) phase of PCIT. Measurements in phase C are identical to those in phase B. After treatment completion, a posttreatment assessment will be performed, which will be identical to the pretreatment assessment. Phase D is the follow-up assessment, which takes place 6 months after treatment completion. The assessment is also identical to the pre- and posttreatment assessments (Figure 2; 10 CDI sessions and 6 PDI sessions are used as a random example).

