Worldwide, dropout rates vary between 12% and 67% [20], and specifically in the Netherlands, studies indicate that there is high attrition and that parents have a hard time grasping the different parenting skills. In that study, 52% of parents who received PCIT dropped out [19]. Attrition rates worldwide seem to be attributed to parenting stress levels and treatment barriers [20]. For instance, single parent status, problem severity of the child, and low socioeconomic status are often attributed to attrition. However, there remains some discrepancy in the literature on what factors contribute to families dropping out, although many studies have attempted to identify predictive factors [21-23]. Nonetheless, one study found that treatment completers reported significantly fewer child behavioral problems and less parental stress at follow-up than treatment dropouts [24]. This indicates that treatment should focus on making parents feel more confident in their parenting, thus potentially diminishing parenting stress and, with that, dropout rates. In further support, a study found that treatment completers showed increasing positive parenting skills and decreasing negative parenting skills from before to after treatment [21]. In addition, positive parenting skills appear to be crucial for improving the parent-child relationship [7]. A meta-analysis on PCIT showed that when meeting the skill criteria is required for completion of treatment, child externalizing behavior is significantly lower than when this is not a requirement [18]. However, when PCIT is offered in a shorter form in community samples (eg, the *standard* 12-session PCIT or the 8-session PCIT-Home), comparable effect sizes can still be yielded for a reduction in disruptive behavior [18,25]. Nonetheless, if skill criteria are met when taking the traditional PCIT protocol into account, PCIT has been shown to make impactful long-term improvements in parental warmth, responsiveness, and effectiveness [17]. In addition, studies have shown that the performance and motivation of a skill can be improved by deliberately practicing that skill [26]. Moreover, parenting programs that incorporate the opportunity to practice new skills with their children are considered more effective interventions than those that do not [27,28]. This suggests that it could be beneficial for parents to practice the skills they learn in the therapy more intensely, thereby potentially reducing dropouts and magnifying the scope of the treatment. It has previously been shown that with live coaching feedback, positive parenting skills increase rapidly, whereas negative parenting behavior decreases rapidly, especially early in the intervention. These results indicate that early interaction change in positive parenting skill acquisition is related to more positive child welfare outcomes [29]. In addition, research indicates that a current obstacle in PCIT is that parents may have a hard time grasping parenting skills, which leads them to drop out because of the inability to fully understand and translate the parenting skills to their home setting [19]. Therefore, to bridge the gap between practicing the (Praise, Reflect, Imitate, Describe, and Enthusiasm [PRIDE]) skills in therapy and applying the skills in a home setting, this study will implement a virtual reality (VR) element. VR allows parents to practice skills regardless of whether their child is home or awake, meaning that the ability to practice skills is on demand whenever they have their smartphone device near them. Over the past years, VR has become increasingly popular within the mental health care sector, as it creates opportunities that would otherwise not be possible [30]. Thus far, research has shown that using technology in PMT programs maintains positive treatment outcomes as long as therapist contact is maintained [31]. Specifically, within PCIT, previously implemented technology augmentations, such as Pocket-PCIT, have been shown to lead to increased treatment completion rates. This indicates a promising development in using technology innovations in an attempt to tackle similar barriers to treatment engagement [28].

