## Methods

### Participants

Children (aged 2-7 years) and their parents will be referred through community channels after seeking help or support. The research will be conducted in clinical practice in the Netherlands, where families first follow a standard intake procedure (which includes an intake interview, completion of a set of questionnaires, and being referred to the right area of expertise) to establish their need for help. After this, families can be included in the study and receive PCIT-VR if the following criteria are met:

Disruptive behavior problems of the child are a reason for referralChildren are aged between 2 and 7 yearsParents speak Dutch or English

A total of 15 families will be included, preferably those who finish the treatment (including all treatment phases and measurement points).

As the design is a SCED, the calculations for the number of participants are based on the What Works Clearinghouse (WWC) [40] and information gained from previous PCIT research. The WWC standards dictate that there are 5 criteria that should be acknowledged in a SCED. One of these criteria states that the minimum number of participants necessary to demonstrate an intervention effect is 3 [41]. In addition, the American Psychological Association [42] states that to display the effectiveness of an intervention, a minimum of 9 replicated single-case studies should be performed. Furthermore, attrition rates according to the standard PCIT ranged between 34% and 77% [43]. Specifically, in the Netherlands, a previous study showed a 40% attrition rate [19]. Therefore, this study will strive to include 15 families, preferably those who finish the entire trajectory to (1) adhere to a minimum of 3 participants according to WWC standards, (2) be able to state that the intervention is effective in accordance with the American Psychological Association guidelines, and (3) compensate for the potential of a 40% attrition rate.

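### Families randomised to VR at the start of CDI give no within-family estimate of what VR adds, yet the sample size counts every completer towards the 9 replications

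*Protocol article*

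**What the plan says.** All of this is in the protocol article.

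- **Question.** Study Design asks whether adding VR raises positive parenting skills. Assessment Instruments makes the DPICS the measure of that primary end point.
- **Randomisation.** Study Design randomises the baseline length (4, 5 or 6 weeks) and "the addition of their VR element (VR at the start of CDI and after 3 or 6 sessions of CDI; phase B"), and adds that families begin PCIT with or without VR according to allocation. It describes the cases as uniform: "This means that 15 individual cases will be analyzed following the same design structure".
- **Measurement.** Weekly phase A data are the ECBI and the short OBVL. The DPICS is first recorded at the single pretreatment assessment, then weekly during PCIT sessions. For phases in general, "a minimum of 3 measurement points is required per phase".
- **Sample size.** Participants gives two benchmarks: "the minimum number of participants necessary to demonstrate an intervention effect is 3", and, for displaying effectiveness, "a minimum of 9 replicated single-case studies should be performed". The target of 15 is meant to meet both and to "compensate for the potential of a 40% attrition rate".
- **Comparison.** Study Design and the Discussion (Principal Findings) stress comparing an individual across phases. They also foresee comparing individuals with one another, including by the timing of VR. The Conclusions treat each participating family as informative about both the treatment and VR.

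**The concern.** A within-family estimate of what VR adds needs sessions of PCIT without VR and sessions with it. A family allocated VR at the start of CDI has only the second kind. Its change from phase A to phase B combines the effect of PCIT with the effect of VR. The article itself describes PCIT as effective and says that positive skills rise quickly early in treatment (Background), so the PCIT share of that change may be large. For the primary end point these families also have no weekly baseline series, only one pretreatment DPICS assessment.

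The sample size makes no allowance for this. It treats each completer as one replicated case. If the effectiveness claim is about what VR adds, the number of within-family replications behind it is smaller than the 9 that the article cites as its basis.

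**Working it through.** **Inputs from the article:** 15 families; 9 replicated cases; lower benchmark 3; attrition 40% (Participants); three VR starts (Study Design). For sensitivity: 34%, the lower end of the standard-PCIT range in Participants, and 52% from Background ("In that study, 52% of parents who received PCIT dropped out"). **Assumption:** one third of families per VR start, because no ratio is given.

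**1. The article's own figure.** N = 9 / (1 − 0.40) = 15, and 15 × 0.60 = 9. It reproduces exactly. Every completer is counted and none is spare.

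**2. Enrolled families with a PCIT-only stretch.** 15 × 1/3 = 5 start VR with CDI, and 15 × 2/3 = 10 start later.

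**3. After attrition, if every dropout is lost to the contrast.** Expected count = 15 × (1 − d) × 2/3.

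| Attrition d | Completers | With a PCIT-only stretch |
|---|---|---|
| 0 | 15 | 10 |
| 34% | 9.9 | 6.6 |
| 40% | 9 | 6 |
| 52% | 7.2 | 4.8 |

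**4. Range at 40%.** The contrast lies within CDI, so a family that leaves during PDI has already supplied it. If all dropouts leave before completing the contrast, the count is 10 × 0.60 = 6. If all leave after CDI, it is 10. Reaching 9 requires that at most 1 of the 10 later-start families is lost before the contrast is complete.

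**5. Other allocation shares, at 40% with all dropouts lost.** Count = 9 × (1 − s), where s is the share starting VR with CDI.
- s = 1/4: 6.75
- s = 1/3: 6
- s = 1/2: 4.5

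Any s above zero puts the expected count below 9. As a measure of the gap, 9 such completers at s = 1/3 would need 9 / (0.60 × 2/3) = 22.5, that is 23 families.

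**6. Chance of reaching 9, on the same pessimistic view of dropouts.**
- Each of 15 families contributes independently with probability 0.60 × 2/3 = 0.40: P(at least 9) = 0.095.
- Every completer counts, probability 0.60: P(at least 9) = 0.61.
- Exactly 10 families allocated to later starts, each completing with probability 0.60: P(at least 9 of 10) = 10 × 0.60⁹ × 0.40 + 0.60¹⁰ = 0.046.

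**7. The late start.** CDI length depends on the skill criteria (Treatment). A family allocated VR after 6 sessions that meets them at session 6 has 6 − 6 = 0 CDI sessions with VR. One that meets them at session 8 has 8 − 6 = 2. Such families lower the count further. By how much cannot be computed, because the article gives no distribution of CDI length; its 10 CDI sessions are labelled a random example.

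**8. Value of the start-of-CDI families as comparators.** A generalised least squares calculation used fixed session effects, 10 CDI sessions, within-family SD 4 with AR(1) correlation 0.3, and between-family SD 4. The standard error of the VR effect is 1.31 skill counts with starts 0/3/6 (5 families each) and 1.84 with the 10 later-start families alone. 1 − 1.31/1.84 = 0.29, so it is 29% smaller. The variances and the 10 sessions are assumed, so this is illustrative only.

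**The case against.** The strongest reply is that an early randomised start is a legitimate arm of a staggered design. This stands. The start-of-CDI families are valid same-session comparators, and the Discussion already foresees comparing individuals by VR timing. It also notes that skill growth slows as families near the criteria, which is a reason to have an early start. A reader might infer that these families cannot show VR's added value at all. That goes too far: what they lack is the within-family contrast.

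Four further inferences are tempting and not supported:

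- **That PCIT's effect will be credited to VR.** No section says the A-to-B change will be reported as a VR effect, and there is no weekly phase A DPICS series on which to base it.
- **That the article breaks its own 3-point rule.** The rule is stated per phase, and the named phases are A to D. The stretches before and after VR starts both lie inside phase B.
- **That the common design structure is contradicted.** All 15 families do share the sequence A to D. They differ only on the VR question.
- **That exactly 6 replications will remain.** Dropouts during PDI may still count, and Participants hopes for finishers ("A total of 15 families will be included, preferably those who finish the treatment"). With 15 finishers, 10 would remain.

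It can also be said that the article never defines a replication as a within-family VR contrast, and that some of its hypotheses concern PCIT-VR as a whole. For the effect of PCIT-VR as a package, every completer does count. That does not settle the matter, because Study Design and Statistical Analysis put the added value of VR first, and for that question the count of 9 is not the right one. An unseen analysis plan could specify the comparison, but it could not create PCIT-only sessions for these families.

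**Conclusion.** The point holds for the within-family contrast. Start-of-CDI families give no within-family estimate of what VR adds, and the sample-size reasoning counts them as if they did. Under equal allocation, about 10 of 15 enrolled families can supply that contrast. At the planned 40% attrition the expected number is between 6 and 10, depending on when dropouts leave, and lower if families allocated to VR after 6 sessions finish CDI before or soon after VR starts. The article relies on 9.

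The shortfall is against the 9-case benchmark only; at 6 the cited minimum of 3 is still met. The result rests on the assumed allocation ratio and on reading a replication as a within-family VR contrast. It should be fixed because a figure that the plan relies on is overstated for its main question. It does not invalidate the randomisation or the design.

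**What to change.** 1. In Participants, state that families allocated VR at the start of CDI do not count towards the 9 for the added value of VR. Restate the expected count (about 6 to 10 under equal allocation, against 9) and say whether families leaving during PDI are included. Word the effectiveness claim to match.
2. State that the A-to-B change in these families is a joint PCIT plus VR effect and will not be read as a VR effect.
3. Analyse them as same-session comparators by randomised VR start. In CDI sessions 1 to 3, compare the start group (VR) with the after-3 and after-6 groups (no VR). In sessions 4 to 6, compare the start and after-3 groups (VR) with the after-6 group (no VR).

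The cost is a less favourable stated count and a modest extra analysis. Enrolment, data collection and the randomisation already done are unchanged.

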### Assessment Instruments

The primary end point of positive parenting skills will be measured using the DPICS [52], and the added value of VR will be measured through VR assessments. Secondary end points, including the psychological functioning of the child, family dynamics and competences, and general therapy evaluation, will be measured through questionnaires and qualitative interviews. This is further explained in the following sections.

The DPICS [52] is a reliable and valid behavioral observational coding system designed to measure the quality of social interactions between parents and children. By coding open verbal and physical behaviors exhibited by both parents and children, the DPICS is able to assess the quality of the parent-child interaction as a construct. Behaviors that are coded are divided into the categories displayed in Textbox 1.

Parent and child behaviors as coded in the Dyadic Parent-Child Interaction Coding System.Parent behaviorsDirect command: compliance, noncompliance, and no opportunity to complyIndirect command: compliance, noncompliance, and no opportunity to complyQuestionBehavioral descriptionReflective statementLabeled praiseUnlabeled praiseNeutral talkNegative talkChild behaviorsNegative talkProsocial talkQuestionCommandWhineYell

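### DPICS, the primary endpoint, has one scheduled point in the randomised baseline against a stated minimum of 3, so the VR effect on it has to rest on the randomised VR start

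*Protocol article*

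**What the plan says.** - **Primary endpoint** (Assessment Instruments): "The primary end point of positive parenting skills will be measured using the DPICS". The same sentence goes on: "the added value of VR will be measured through VR assessments". VR Evaluation lists these assessments as user analytics, a completion sheet and parent interviews.
- **Design rule** (Study Design): "a minimum of 3 measurement points is required per phase". The rule sits in the account of what makes a SCED strong, and the section says those dimensions are built into this study.
- **Phase A** (Study Design): families are randomised to "determine their baseline period (4, 5, or 6 weeks of baseline measurements; phase A". The weekly measures are questionnaires: "Parents will electronically fill out the questionnaires weekly regarding child disruptive behaviors and parental stress using the ECBI" and the OBVL-K. DPICS enters only afterwards: "At the end of phase A, a pretreatment assessment will be performed". That assessment includes a recording of three play situations coded with the DPICS.
- **Phase B** (Study Design): phase B is the CDI part of PCIT, with or without VR. A second randomisation sets VR to begin at CDI start or after 3 or 6 CDI sessions. Therapists code DPICS weekly in sessions.
- Assessment Instruments agrees with this schedule: DPICS is scored during treatment and at the pretreatment, posttreatment and follow-up assessments.

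**The concern.** A multiple baseline design draws its strength from a repeated series of the outcome before the change and from a randomised moment of change. Here the repeated baseline series exists for two secondary outcomes and not for the primary one. With a single value, DPICS has no baseline trend or variability, and a randomisation test on baseline length has no DPICS values at the alternative start weeks.

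The labelled phases also do not isolate VR. The step from A to B is the start of PCIT, and in the VR-at-start families it is the start of PCIT and VR together. If the labelled phases were analysed as they stand, and VR's added value were read from analytics, completion sheets and interviews, the report could present an effect of PCIT on questionnaires alongside usage data. It would then contain no comparison of parenting skill with and without VR, which Study Design gives as the aim.

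**Working it through.** **1. The plan's own figure.** Participants gives a minimum of 9 replicated cases and 40% attrition: 9 / (1 − 0.40) = 15 families, and 15 × 0.60 = 9 completers. The stated 15 is reproduced, and nothing below changes it.

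**2. Scheduled points in phase A** (Study Design)

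| Baseline drawn | Weekly ECBI | Weekly OBVL-K | DPICS occasions | Stated minimum |
|---|---|---|---|---|
| 4 weeks | 4 | 4 | 1 | 3 |
| 5 weeks | 5 | 5 | 1 | 3 |
| 6 weeks | 6 | 6 | 1 | 3 |

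The DPICS count does not depend on the length drawn. The three play situations are different tasks on one occasion, so they are not three points in time.

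**3. VR-free DPICS points by randomised VR start**, for families still in CDI at that session

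| VR start | In-session, VR-free | Plus pretreatment | At least 3 in-session? |
|---|---|---|---|
| CDI start | 0 | 0 + 1 = 1 | No |
| After 3 sessions | 3 | 3 + 1 = 4 | Yes |
| After 6 sessions | 6 | 6 + 1 = 7 | Yes |

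Both delayed arms meet the minimum from in-session scores alone. In the article's illustrative course of 10 CDI sessions, sessions with VR would number 10, 10 − 3 = 7 and 10 − 6 = 4.

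**4. Families per arm.** The allocation ratio is not stated. If it is equal, 15 / 3 = 5 families per arm, or 9 / 3 = 3 completers per arm with even attrition. About 5 of 15 families then have no VR-free CDI session, and the within-family contrast rests on the other 10 (6 of 9 completers).

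**5. What VR-at-start families can add.** They can be compared with delayed families at the same session number. With 5 per arm, all still in CDI:

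| CDI session | With VR | Without VR |
|---|---|---|
| 1–3 | 5 | 10 |
| 4–6 | 10 | 5 |
| 7 onward | 15 | 0 |

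The between-family information on VR lies in the first six sessions.

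**6. Order.** Within a delayed family the VR-free sessions always come first. The Discussion (Principal Findings) says skill growth slows as families approach the criteria. A plain before-and-after comparison would confuse VR with that curve, so a session trend is needed.

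**The case against.** A reader might infer that the primary question cannot be answered at all. The documents do not support that. The question is the added value of VR, and its randomisation falls in phase B, where DPICS is weekly. Nowhere is A-versus-B named as the primary DPICS test. Statistical Analysis lists SCED, repeated measures and graphical analyses, and the Discussion already expects outcomes to show whether VR timing matters. An article may leave the exact contrast to a fuller document.

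It can also be said that the three-point rule is general and set per phase, not per outcome, so that 4 to 6 weekly questionnaires satisfy its letter. That reading is possible, but it gives the primary endpoint no baseline series.

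Two further readings go too far. One is that usage data and opinions wholly replace a test of VR. The clause on VR assessments is loosely worded and shares its sentence with the DPICS, and the analytics also record parents' answers. The other is that the pretreatment DPICS is on an entirely different basis from the weekly scores. Both use the same instrument over 5-minute observations; what differs is the setting, the tasks and who records or codes.

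What stands is the schedule. Measurement timing is design, and no analysis plan can create phase A DPICS points that were never collected. The sentence assigning VR's added value to VR assessments is in the article itself and conflicts with the aim in Study Design.

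**Conclusion.** The point holds in limited form. Every family has 1 scheduled DPICS occasion in phase A against a stated minimum of 3, so the 4, 5 or 6-week randomisation cannot support SCED inference on the primary endpoint. It does support the ECBI and OBVL-K. A test of VR on DPICS remains available from the randomised VR start, with 3 or 6 VR-free in-session points in the delayed arms, but the article does not name it and points to VR assessments instead.

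The count of 1 comes from the text of Study Design and Assessment Instruments; the figures were not available. The count of about 5 families without VR-free CDI sessions assumes equal allocation. The 3 and 6 points assume that families stay in CDI at least that long.

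**What to change.** 1. State that the primary contrast is weekly in-session DPICS positive skills in CDI without versus with VR, keyed to the randomised VR start and modelled with a session trend.
2. State that families with VR at CDI start have no VR-free CDI sessions and contribute only through comparison with delayed-start families at the same session number. State the allocation ratio.
3. Limit baseline-length (A-versus-B) inference to ECBI and OBVL-K. Label it an effect of starting PCIT, or of PCIT plus VR in the VR-at-start families, and not of VR alone.
4. Reword the Assessment Instruments sentence so that VR assessments are usage and experience outcomes.

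**Cost.** These are wording changes to the protocol and analysis, using measurements already scheduled. Six families were enrolled at submission and completion was projected for 2023, so the contrast should be fixed before analysis.

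**Downside.** The within-family VR contrast rests on delayed-start families only, and the baseline randomisation no longer supports a claim on the primary endpoint. The fix adds no DPICS points to phase A; repeated DPICS there would meet the minimum (4 to 6 points if weekly) but needs new data collection.
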